#### Proportion of subjects with motion pain relief

In addition, since pain with motion is generally uncontrollable, it would be clinically significant to demonstrate an improvement in this variable with TAE. The proportion of subjects with decreased pain with motion will be assessed based on the BPI-SF questionnaire. It will be comprehensively determined based on the improvement in maximum pain measured by Item 3 and the improvement in motion measured by Item 9.

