#### Inclusion criteria

Patients fulfilling all the following criteria will be eligible for inclusion in this study:1) Diagnosis of painful bone metastases (multiple metastases are acceptable)2) The most painful bone metastases involve the thoracic spine, lumbar spine, pelvis, or rib(s), for which arterial embolization is expected to relieve pain3) No evidence of spinal cord compression on CT or MRI scan of the most painful bone metastases4) Numerical rating scale (NRS) score of ≥ 5 (Max10) for bone metastatic pain5) Current use of opioid analgesics6) No radiotherapy (RT) at the planned site(s) of TAE within the preceding 3 months7) No initiation of new chemotherapy or hormone therapy within the preceding 2 weeks8) Patients with any cancer9) Life expectancy > 1 month10) Normal renal function and no bleeding risk11) Age ≥ 20 years12) Ability to provide written informed consent to participate in the study

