#### Proportion of subjects with pain relief at 24 h/7 days/14 days after arterial embolization

To investigate the timing, course, and duration of pain relief in response to arterial embolization, the proportions of subjects with pain relief at 24 h, 7 days, and 14 days are included as other secondary endpoints. The proportion of subjects with pain relief will be assessed based on the Brief-Pain Inventory-Short Form (BPI-SF) questionnaire [15].

The proportion of subjects with pain relief will be calculated using the following equation:3$$proportion of subjects with pain relief = (complete response + partial response)/(FAS - subjects with missing data)$$

where “FAS” stands for “Full Analysis Set,”

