### Participant timeline

Patients will be registered online before the TAE protocol is initiated.

After protocol treatment starts, several evaluations for pain and a general examination will be performed at 24 h, 72 h, 7 days, and 14 days after protocol treatment. The assessment schedule from enrollment to 2 weeks after protocol treatment is shown in Table 2.

**Table 2 Tab2:** Time Schedule

	Pretreatment	Arterial embolization	24 h (± 3 h)	72 h (± 3 h)	7 d (± 1 d)	14 d (± 2 d)
Karnofsky Performance Status (KPS)	〇		〇	〇	〇	〇
Numerical rating scale (NRS)	〇					
Brief Pain Inventory			〇	〇	〇	〇
Quantity of morphine used per day	〇		〇	〇	〇	〇
Blood exam	〇		〇			
CTCAE ver 5.0 (safety profile)		〇	→ always checked →			〇

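### Motion-pain relief is defined as improvement on the BPI-SF, but Table 2 schedules the BPI only after TAE: Item 9 has no baseline, and pain-intensity change would cross two instruments

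*Protocol article*

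**What the plan says.** All references are to the protocol article.

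- **Motion-pain relief** (Proportion of subjects with motion pain relief). The instrument is the BPI-SF: "The proportion of subjects with decreased pain with motion will be assessed based on the BPI-SF questionnaire". The judgement combines "improvement in maximum pain measured by Item 3 and the improvement in motion measured by Item 9".
- **Pain relief at 24 h, 7 days and 14 days** (section of that name). "The proportion of subjects with pain relief will be assessed based on the Brief-Pain Inventory-Short Form (BPI-SF) questionnaire".
- **Primary endpoint** (Endpoints, Efficacy). Pain relief at 72 h, with a responder being a CR or PR under the international consensus for palliative radiotherapy trials. This section names no pain instrument and no baseline.
- **Schedule** (Participant timeline). "The assessment schedule from enrollment to 2 weeks after protocol treatment is shown in Table 2". In that table the row "Brief Pain Inventory" is marked at 24 h, 72 h, 7 d and 14 d, and its pretreatment cell is empty. The NRS row is marked at pretreatment and nowhere else. The accompanying text agrees: "several evaluations for pain and a general examination will be performed at 24 h, 72 h, 7 days, and 14 days after protocol treatment".
- **Entry criterion** (Inclusion criteria). "Numerical rating scale (NRS) score of ≥ 5 (Max10) for bone metastatic pain".

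**The concern.** An improvement is a change, and a change needs the same quantity measured before and after. In Table 2 no pain instrument appears on both sides of TAE. Two consequences follow if the table is carried out literally.

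First, Item 9, the motion component of motion-pain relief, has no pretreatment counterpart. The pretreatment NRS is a pain score and cannot stand in for it.

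Second, any change in pain intensity would have to be formed from an NRS reading before TAE and a BPI item after it. The article does not say which BPI item or recall period corresponds to that NRS. In a randomised comparison an offset between two measures would largely cancel between arms. Here there is one arm and a fixed threshold, so an offset would be indistinguishable from a treatment effect, or would hide one.

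**Working it through.** **Step 1. The schedule against the endpoints.** The relevant rows of Table 2:

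| Row | Pretreatment | 24 h | 72 h | 7 d | 14 d |
|---|---|---|---|---|---|
| KPS | yes | yes | yes | yes | yes |
| NRS | yes | – | – | – | – |
| BPI | – | yes | yes | yes | yes |
| Daily morphine quantity | yes | yes | yes | yes | yes |

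The four follow-up marks in the BPI row line up with those in the KPS and morphine rows, and only the pretreatment mark is absent. A shifted or broken row is therefore an unlikely explanation. The table's stated span begins at enrollment, so a baseline assessment falls within its scope. No other section mentions a pretreatment BPI.

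**Step 2. What each endpoint needs and what is scheduled.**

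| Quantity | Before TAE | After TAE | Computable as scheduled? |
|---|---|---|---|
| Item 9 (motion) change | nothing | BPI Item 9 | No, for any subject |
| Item 3 (maximum pain) change | NRS only | BPI Item 3 | Only across instruments |
| CR/PR at 24 h, 7 d, 14 d | NRS only | BPI-SF (stated) | Only across instruments |
| CR/PR at 72 h (primary) | NRS only | BPI (the only pain score marked) | Probably only across instruments |

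The last row is an inference from Table 2, because the Efficacy section does not name the instrument.

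**Step 3. The plan's own figure.** The Sample size section uses 26% against 40%, one-sided 2.5% and 90% power, by normal approximation:

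n = [(1.960·√(0.26·0.74) + 1.282·√(0.40·0.60)) / (0.40 − 0.26)]² = 112.90, rounded up to 113.

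This agrees with the stated 113. The point here does not change it. It only supplies the scale: the designed difference is 14 percentage points.

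**Step 4. Illustration of an offset.** Nothing in the article gives an offset, an SD of change or a points rule, so all three are assumed: response is a fall of at least a fixed number of points, change scores are roughly normal, their SD is 2, 2.5 or 3, and the two measures differ systematically by 1 point. For a true rate p, let z_p satisfy P(Z > z_p) = p. The apparent rate is P(Z > z_p − 1/SD) if the offset favours response, and P(Z > z_p + 1/SD) if it works against it. For 26%, z_p = 0.643; for 40%, z_p = 0.253.

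| SD of change | True 26%, favourable offset | True 26%, unfavourable offset | True 40%, unfavourable offset |
|---|---|---|---|
| 2 | 44.3% | 12.6% | 22.6% |
| 2.5 | 40.4% | 14.8% | 25.7% |
| 3 | 37.8% | 16.4% | 27.9% |

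Under these assumptions a 1-point offset moves the apparent rate by roughly 10 to 18 points, which is of the same order as the designed 14.

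**The case against.** The strongest reply is that the article condenses a longer protocol, and an empty cell that conflicts with the endpoint definitions may be a slip in the table and not a gap in data collection. That is possible, and the article cannot settle it. So a reader should not conclude that the BPI is never collected before treatment. But the article prints a complete schedule that disagrees with its own endpoints, and one of the two has to be corrected.

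It can also be said that nothing states outright that the 72 h response compares an NRS with a BPI score. This is right. The BPI-SF sentence belongs to the 24 h, 7 day and 14 day endpoints, and the reach to 72 h rests on Table 2 alone. Likewise, nothing shows that the pretreatment NRS is worded differently from BPI Item 3. If the wording matches, the pain-intensity part becomes less serious. Item 9 would still have no baseline.

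Two stronger readings are tempting, and the document does not support them:

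- **That one point of offset creates or erases the whole designed effect.** The offset, the SD and the responder rule are assumptions, and even on those terms the statement fails in some cases. At SD 3 a true 26% reaches only 37.8%, and a true 40% falls only to 27.9%, still above 26%. Daily morphine is also recorded before and after TAE, so response may not depend on the pain score alone.
- **That the NRS entry threshold of 5 builds regression to the mean into the result.** The article does not say that the entry reading is also the analysis baseline. Any bias against the 26% benchmark would depend on how the cited radiotherapy study selected its patients, which cannot be seen here.

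**Conclusion.** The inconsistency between Table 2 and the endpoint definitions is established on the face of the document. As scheduled, Item 9 change is available for none of the subjects, so motion-pain relief cannot be derived as defined. Pain-intensity change has only a cross-instrument baseline. Extension to the primary 72 h endpoint is probable but inferred.

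The effect on the response rate tested against 26% cannot be sized from the document, and neither its direction nor its existence is known. The illustrated ranges (38%–44% or 13%–16% for a true 26%) show only that an offset of a single point, if present, would matter in this design.

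It needs correction either way: if a pretreatment BPI is taken, the table is wrong; if it is not, one secondary endpoint lacks its data and the baseline for pain response needs to be defined.

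**What to change.** 1. Reconcile Table 2 with the Efficacy section, the 24 h/7 days/14 days section and the motion-pain section.
2. If a pretreatment BPI-SF is already collected, mark it in Table 2. If it is not, add the BPI-SF at pretreatment, before TAE.
3. State that CR/PR uses the same BPI pain item before and after TAE, and name that item. State that motion-pain relief uses baseline Items 3 and 9. Keep the screening NRS for eligibility.
4. For subjects already treated without a baseline BPI, use the pretreatment NRS as the pain baseline, report response by baseline instrument as a sensitivity analysis, and restrict the Item 9 endpoint to subjects who have a baseline.

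**Cost.** One more short questionnaire on the ePRO system already in use, and a schedule amendment. A missing baseline cannot be recovered afterwards. The article reports 36 participants by August 2022 out of 120 planned (36/120 = 30%). If the table was followed literally, up to those 36, plus anyone treated before the amendment, would be lost to the Item 9 endpoint, leaving at most 120 − 36 = 84 subjects for it.

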### Participant timeline

Patients will be registered online before the TAE protocol is initiated.

After protocol treatment starts, several evaluations for pain and a general examination will be performed at 24 h, 72 h, 7 days, and 14 days after protocol treatment. The assessment schedule from enrollment to 2 weeks after protocol treatment is shown in Table 2.

**Table 2 Tab2:** Time Schedule

	Pretreatment	Arterial embolization	24 h (± 3 h)	72 h (± 3 h)	7 d (± 1 d)	14 d (± 2 d)
Karnofsky Performance Status (KPS)	〇		〇	〇	〇	〇
Numerical rating scale (NRS)	〇					
Brief Pain Inventory			〇	〇	〇	〇
Quantity of morphine used per day	〇		〇	〇	〇	〇
Blood exam	〇		〇			
CTCAE ver 5.0 (safety profile)		〇	→ always checked →			〇

### Sample size

The clinical hypothesis is that patients with painful bone metastases can be safely treated with arterial embolization for immediate pain relief.

The early response rate after arterial embolization must exceed that after radiotherapy in order for arterial embolization to be established as a new palliative therapy. Since the early response rate was reported to be 26% at 1 week after radiotherapy [16], it is assumed to be lower at 72 h after radiotherapy.

Assuming that the threshold for the proportion of subjects with pain relief at 72 h after arterial embolization, i.e., the primary efficacy endpoint, is 26%, and the expected response rate is 40%, which represents the minimum clinical utility, at least 113 patients are required to provide a power of 90% at a one-sided significance level of 2.5% (normal approximation test).

On the other hand, an adverse event associated with TAE, which is the primary safety endpoint, is defined as any CTCAE Grade 4 adverse event or Grade ≥ 3 CNS necrosis. As described in “Common Adverse Events Associated with Arterial Embolization,” adverse events (including mild events) have been reported in 5% to 7% of patients who undergo arteriography, 10% of patients treated with arterial embolization, and approximately 15% of patients treated with TACE. Considering that patients in poor general condition will be included in this study, the unacceptable threshold incidence for the clinical use of this treatment is set at 15%, equal to that for TACE for hepatocellular carcinoma [17]. Assuming that the incidence will actually be approximately 5% in this study where no anticancer drugs will be used concomitantly; and that bones will be treated, at least 96 patients are required to provide a power of 90% at a one-sided significance level of 2.5% (normal approximation test) (Fig. 1).

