**Fig. 1 Fig1:**
[figure not shown]
Study schema this study consists of two sections, the exploratory and confirmatory phases. Registration will be suspended when 20 subjects are recruited to analyze the data set rather than investigate all the events individually. (Stopping rule) Recruitment of a total of 120 patients is planned

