### Safety (secondary endpoint)

The secondary endpoint (safety) is the incidence of all CTCAE Grade 4 adverse events and CTCAE Grade ≥ 3 CNS necrosis associated with the arterial embolization procedure.

In this study, the incidence of all CTCAE Grade 4 adverse events and CTCAE Grade ≥ 3 CNS necrosis associated with the arterial embolization procedure will be assessed in the 2-week post-TAE observation period.

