### Statistical methods of analysis

As defined in the Section “Primary Endpoints,” the proportion of subjects with pain relief 72 h after arterial embolization and its two-sided 95% confidence interval (Clopper-Pearson method) will be calculated. It will be determined whether the lower limit of the two-sided 95% confidence interval is > 26%, the threshold response rate established at the time of study design. For reference, the *p*-value will be calculated by a binomial test.

Safety will be evaluated in the Safety Analysis Set (SAS) (Table 2). As defined in “Safety,” the incidence of all CTCAE Grade 4 adverse events and CTCAE Grade ≥ 3 adverse events of CNS necrosis associated with TAE and its two-sided 95% confidence interval (CI) (Clopper-Pearson method) will be calculated. It will be determined whether the upper limit of the two-sided 95% CI is < 15%, the threshold incidence established at the time of study design. For reference, the *p*-value will be calculated by a binomial test.

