## Discussion

In this study, we will examine the effect of TAE in providing immediate pain relief (within 3 days) for painful bone metastases. Palliative radiotherapy is one of the most commonly used modalities for painful bone metastases; however, its median time to pain relief is 4–8 weeks. Painkillers, including opioid analgesics, temporarily relieve pain but do not remove its cause. Therefore, a modality which can achieve immediate pain relief and remove its cause is necessary in this field. TAE may have the potential to achieve these goals.

Since there is no standard treatment to compare with TAE for relieving bone metastatic pain in as short as a few days, this study will be conducted with a single arm. Because no quickly effective standard treatment is available, TAE, if shown to be quickly effective, will serve as a useful treatment option in clinical practice. In that case, TAE will be practically handled as one of several standard approaches; therefore, this study will be conducted as a confirmatory study. The study will also be conducted as a single-arm confirmatory study without controls in accordance with the Research Policy of Supportive and Palliative Care in Japan [18].

Because TAE’s safety and efficacy have not been confirmed in a palliative setting, a prospective confirmatory trial is needed. Considering that palliative radiotherapy, pain killers, and TAE can be combined, we feel a randomized control study design comparing TAE with these other modalities is not necessary. In order to preserve the reliability of the results, we will evaluate efficacy and safety by maintaining strict thresholding and stopping rules.

TAE is not a major tool in this field at present. If the primary and co-primary endpoints are met, TAE can be a treatment choice for painful bone metastases, and these results will potentially provide many benefits for all eligible patients with painful bone metastases.

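### The 90% power is for a normal-approximation test, but success is decided on Clopper-Pearson limits; under that rule efficacy power is about 86% at 113 patients and 89% at 120

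*Protocol article*

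**What the plan says.** **Sizing (Sample size section).** The efficacy null value is given by "Assuming that the threshold for the proportion of subjects with pain relief at 72 h after arterial embolization, i.e., the primary efficacy endpoint, is 26" (per cent). For the alternative, the text says that "the expected response rate is 40%, which represents the minimum clinical utility". The resulting claim is "at least 113 patients are required to provide a power of 90% at a one-sided significance level of 2.5% (normal approximation test"). For safety, "the unacceptable threshold incidence for the clinical use of this treatment is set at 15"%, the assumed true incidence is about 5%, and 96 patients are said to be enough at the same power, one-sided level and type of test. The caption of Fig. 1 adds: "Recruitment of a total of 120 patients is planned".

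**Decision rule (Statistical methods of analysis).** Each proportion gets a two-sided 95% Clopper-Pearson interval. For efficacy, "It will be determined whether the lower limit of the two-sided 95% confidence interval is > 26"%. For safety, the upper limit must lie below 15%. The binomial p-values are for reference only.

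**Status of the safety endpoint.** The Abstract and the section headed "Safety (secondary endpoint") treat it as secondary. The Sample size section calls the same endpoint primary for safety. The Discussion makes its conclusion depend on both: "If the primary and co-primary endpoints are met". The Abstract does the same, but with safety named as secondary.

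**The concern.** The quoted power belongs to a test that the trial will not use for its decision. A Clopper-Pearson limit is conservative, so it can require more responders (or allow fewer events) than the normal approximation at the same sample size. A reader who takes 90% at 113 patients as the chance of success under the protocol's own rule is then misled.

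A second question follows. If a positive conclusion needs efficacy and safety together, the relevant chance is that of meeting both, and the protocol does not give it. Whether both are needed is unclear because the safety endpoint carries three different labels. That matters most if one endpoint is met and the other is not.

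**Working it through.** **Inputs.** All come from the Sample size section except the 120 (Fig. 1) and the Clopper-Pearson rule (Statistical methods of analysis). Efficacy: p0 = 0.26, p1 = 0.40. Safety: p0 = 0.15, p1 = 0.05. One-sided level 0.025 (z = 1.960), power 0.90 (z = 1.2816).

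**1. Reproduce the stated sizes.** n = [z(0.975)·√(p0(1−p0)) + z(0.90)·√(p1(1−p1))]² / (p1−p0)².

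- Efficacy: (0.8597 + 0.6278)² / 0.14² = 112.9, so 113.
- Safety: (0.6998 + 0.2793)² / 0.10² = 95.9, so 96.

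Both match the protocol.

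**2. Cut-offs under the Clopper-Pearson rule.** The lower limit for x of n is the 0.025 quantile of Beta(x, n−x+1). The upper limit is the 0.975 quantile of Beta(x+1, n−x).

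- Efficacy, n = 113: 39 responders give a lower limit of 25.8% (fail), and 40 give 26.6% (pass). The normal test already passes at 39, with z = (39/113 − 0.26)/√(0.26·0.74/113) = 2.06.
- Efficacy, n = 120: 41 give 25.8% (fail), 42 give 26.5% (pass).
- Safety: the upper limit stays below 15% with at most 7 events of 96 (14.4%), 9 of 113 (14.6%) or 10 of 120 (14.8%).

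**3. Exact binomial power.**

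| Endpoint | n | Rule | Power | Exact one-sided error |
|---|---|---|---|---|
| Efficacy, true 40% | 113 | ≥ 40 | 0.8635 | 0.0171 |
| Efficacy, true 40% | 120 | ≥ 42 | 0.8877 | 0.0181 |
| Safety, true 5% | 96 | ≤ 7 | 0.892 | 0.0178 |
| Safety, true 5% | 113 | ≤ 9 | 0.943 | 0.0189 |
| Safety, true 5% | 120 | ≤ 10 | 0.962 | 0.0217 |

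Efficacy power for n = 113, 114, …, 120 is 0.8635, 0.8788, 0.8927, 0.8687, 0.8834, 0.8968, 0.8736 and 0.8877. It first reaches 0.90 at n = 121. Because it moves in a sawtooth, it stays above 0.90 only from n = 130.

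For comparison, the normal test at n = 113 (cut-off 39) has exact power 0.902, but its exact one-sided error is 0.0277, above 0.025.

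**4. Both endpoints, if both are required.** The protocol gives no correlation, so independence is an assumption. The bounds P(A) + P(B) − 1 and min(P(A), P(B)) cover any dependence.

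- n = 113: 0.8635 × 0.9429 = 0.814; bounds 0.806 to 0.864.
- n = 120: 0.8877 × 0.9616 = 0.854; bounds 0.849 to 0.888.

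Counting the safety stop at 4 or more of the first 20 (probability 1.6% at a true 5%), the independent values become about 0.805 and 0.843.

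**The case against.** **The arithmetic is correct.** The protocol names its test, and 113 and 96 are right for it. Sizing by a normal approximation and reporting exact limits is common, and the exact rule keeps the one-sided error below 2.5%. This stands. The fault is that the sizing test and the decision rule differ, although the protocol states both explicitly.

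**The gap is small at the planned size.** At 120 evaluable patients efficacy power is 1.2 points short. The value at 113 is a sawtooth trough; at 112 it is 0.8885 and at 115 it is 0.8927. The 40% is also described as a minimum useful rate, and at a true 45% exact power is about 98% to 99%. All of this stands and limits the severity. It does not rescue the stated figure, because no n from 113 to 120 reaches 90%. The 88.8% also needs all 120 to be evaluable, whereas Table 1 removes ineligible and untreated patients from the full analysis set and no imputation is planned in principle.

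**Joint power.** A reader might infer that the protocol promises a 90% chance of meeting both endpoints and delivers only 81% to 85%. The document does not support that. It states one power per endpoint and no joint figure, it tests each endpoint separately without a combined success rule, and in two places it calls safety secondary. The denominators can differ as well. The pain-relief equation, given for the other time points, uses the full analysis set less missing data, while safety uses everyone treated. With 113 evaluable for efficacy and 120 for safety, the joint value is 0.8635 × 0.9616 = 0.830. Joint power is therefore a consequence that applies if both endpoints are required, and not a second wrong figure.

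**Conclusion.** The point holds for each endpoint taken separately. Under the rule that decides the trial, 113 patients do not give 90% efficacy power. They give about 86%, a shortfall of 90 − 86.35 = 3.65 points. At 120 the figure is about 89%, a shortfall of 1.2 points. Safety is just short at its own stated size (89.2% at 96) and comfortable at 113 and 120 (94.3% and 96.2%). These results rest only on the protocol's own rates and on the stated n being evaluable.

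The joint figures of about 81% and 85% also need both endpoints to be required and to be independent. The Abstract and the Discussion point towards both being required, while the secondary labels point the other way.

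Severity is moderate. A reader might conclude that the trial is materially underpowered or must be enlarged. A 1.2-point gap at 120, at a rate described as the minimum of clinical utility, does not support that, and the risk of a false positive finding is not increased.

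**What to change.** 1. Keep the Clopper-Pearson rule. Switching to the normal test would restore the 90%, but with an exact one-sided error of 2.8% at 113.
2. Restate power in the Sample size section for that rule: about 86% at 113 and 89% at 120 evaluable patients for efficacy; about 89% at 96, 94% at 113 and 96% at 120 for safety.
3. Give the decision counts as a function of the evaluable number actually achieved in each analysis set. At least 42 responders of 120 and at most 10 events of 120 serve only as the example for full enrolment with nobody excluded or missing.
4. Have the sponsor settle one label for the safety endpoint, use it throughout, and say whether both endpoints are required for a positive conclusion. If they are, add joint power of about 81% at 113 and 85% at 120, with the independence assumption and the bounds (81% to 86% and 85% to 89%).

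The cost is wording only. The stated power becomes somewhat less favourable. No extra patients are needed, and the thresholds and the analysis do not change.

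### The 15% safety limit comes from a TACE adverse-event rate described as including mild events, but it is applied to Grade 4 events and Grade ≥ 3 CNS necrosis

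*Protocol article*

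**What the plan says.** All the relevant statements on the benchmark stand in one paragraph of the protocol article, under Sample size.

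- **Endpoint.** The safety event "is defined as any CTCAE Grade 4 adverse event or Grade ≥ 3 CNS necrosis".
- **Reference rates.** The next sentence reports that "adverse events (including mild events) have been reported in 5% to 7% of patients who undergo arteriography", and continues with "10% of patients treated with arterial embolization, and approximately 15% of patients treated with TACE".
- **Limit.** "the unacceptable threshold incidence for the clinical use of this treatment is set at 15%, equal to that for TACE for hepatocellular carcinoma". The only further consideration offered is "Considering that patients in poor general condition will be included in this study".
- **Expected rate and size.** "Assuming that the incidence will actually be approximately 5% in this study where no anticancer drugs will be used concomitantly", and that bones are the target, "at least 96 patients are required to provide a power of 90% at a one-sided significance level of 2.5% (normal approximation test").

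Statistical methods of analysis turns the limit into the decision rule, using the Clopper-Pearson interval in the safety analysis set: "It will be determined whether the upper limit of the two-sided 95% CI is < 15" per cent. The caption of Fig. 1 gives a planned total of 120 patients.

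**The concern.** The reference rates count adverse events of every severity; the endpoint counts only the most severe. Severe events are a subset of all events, so a TACE rate that includes mild events is at least as large as the TACE rate of the severe composite. Using the first as the ceiling for the second makes the ceiling too high if any of the counted TACE events were mild.

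This matters more than usual because there is no control arm. The Discussion relies on strict thresholds and stopping rules to keep the results reliable, and makes the conclusion depend on meeting both the efficacy and the safety endpoint. The 15% figure therefore carries the safety half of the conclusion. If it does not measure the same kind of event as the endpoint, meeting it does not show that severe toxicity compares acceptably with TACE.

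**Working it through.** **Inputs.** Limit p0 = 0.15, expected rate p1 = 0.05, one-sided α = 0.025 and power 0.90 (Sample size); upper two-sided 95% Clopper-Pearson limit below 15% (Statistical methods of analysis); n = 120 (Fig. 1 caption). The probabilities below assume that all 120 are treated and so belong to the safety analysis set.

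**Step 1: the plan's own figure.** The one-sample normal approximation is

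n = [(z₀.₉₇₅·√(p0(1−p0)) + z₀.₉₀·√(p1(1−p1))) / (p0−p1)]²

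= [(1.960·√0.1275 + 1.282·√0.0475) / 0.10]² = [(0.6998 + 0.2793) / 0.10]² = 95.87, rounded up to 96.

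This is the stated number. The arithmetic is sound; the question is where 0.15 comes from.

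**Step 2: what the rule accepts.** The upper limit for x events in n patients is the 0.975 quantile of a Beta(x+1, n−x) distribution.

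| n | Most events that pass | Observed rate | Upper limit |
|---|---|---|---|
| 96 | 7 | 7.3% | 14.4% |
| 113 | 9 | 8.0% | 14.6% |
| 120 | 10 | 8.3% | 14.8% |

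At n = 120, 11 events give an upper limit of 15.8% and fail.

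**Step 3: probability of passing at n = 120.** This is P(X ≤ 10) for X ~ Binomial(120, p).

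| True severe rate p | 5% | 6% | 7% | 8% | 10% | 12% | 15% |
|---|---|---|---|---|---|---|---|
| P(pass) | 96% | 89% | 78% | 64% | 34% | 13% | 2.2% |

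The last column is the exact type I error, so the test is valid against 15%. The 10% column is the case where the severe rate alone equals the whole all-severity rate quoted for embolization.

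**Step 4: the interim stopping rule.** Under Study setting the trial stops if at least 4 of the first 20 patients have such an event. Passing then needs at most 3 events in the first 20 and at most 10 in all 120:

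Σ (k = 0 to 3) P(X₂₀ = k)·P(X₁₀₀ ≤ 10−k)

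This is 62% at p = 8% and 32% at p = 10%, so the stopping rule changes little.

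**Step 5: how much too high the limit is.** If a share s of the quoted 15% were severe, the like-for-like TACE rate would be 0.15·s. The document gives no s. Purely assumed values of 10%, 20%, 33% and 50% give 1.5%, 3%, 5% and 7.5%. The direction is fixed (s ≤ 1); the size is not.

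**The case against.** The strongest reply has five parts.

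1. *The source may report serious complications.* The limit carries its own citation, and the reference rates are attributed to a section of the full protocol that the article does not reproduce. The link is therefore read from adjacent sentences and a matching number. This stands as a limit on the claim: a reader might infer that the safety test is far too lenient, and the document cannot support that, because it gives no severe-event rate for TACE or for embolization. It does not remove the point. The only description in the text is that mild events are included; if the cited source differs, the text needs correcting.

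2. *A tolerable rate is partly a clinical judgement, and frail patients justify an allowance.* A judgement would be legitimate, but the protocol presents the figure as equal to a TACE benchmark. Poor general condition is the reason for choosing that figure; it does not convert an all-severity rate into a severe one.

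3. *The rule is stricter than observing less than 15%.* This stands. The whole interval must lie below 15%, and a true rate of 10% fails about two times in three.

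4. *The expected 5% is reasonable.* This stands. A reader might infer that 5% is wrong because it is half the 10% quoted for embolization. A severe-event rate should lie below the all-severity rate, and the protocol gives reasons for it: no anticancer drugs, and bone as the target.

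5. *Other safeguards exist.* Adverse events are checked throughout, and Grade ≥ 2 incidence is reported as a secondary endpoint. Severe toxicity will be visible whatever the verdict, but this does not supply a rationale for 15%.

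**Conclusion.** The point holds as a mismatch between benchmark and endpoint. As written, the protocol takes its limit from a TACE rate that includes mild events and applies it to a severe composite. A like-for-like limit cannot exceed 15% and is lower if any of those TACE events were mild; the document does not allow the excess to be computed.

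What can be computed is what the rule permits: up to 10 severe events in 120, with the pass probabilities of 64% and 34% shown above at true rates of 8% and 10%. These rest on 120 treated patients and the stated Clopper-Pearson rule. They describe the rule's behaviour; they do not show that such rates are likely.

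The sample-size arithmetic is correct and the test is valid against 15%. What is unsupported is any conclusion that meeting this limit makes severe toxicity acceptable by reference to TACE.

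**What to change.** **Preferred change.** Derive the limit from the rate, in the TACE source already cited, of the same composite: Grade 4 events or Grade ≥ 3 CNS necrosis, or the nearest serious-complication category reported. The Grade 3 CNS-necrosis component must stay in, otherwise a new mismatch arises. Then restate the expected rate and the power at n = 120, without adding patients.

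**If the source gives no such rate.** Remove the statement that the limit equals the TACE figure. Report the composite incidence with its already planned Clopper-Pearson interval, and do not conclude from an upper limit below 15% that severe toxicity is acceptable or comparable to TACE.

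Applying 15% to all-grade events instead would not be a sound repair. The section on permitted concomitant therapies anticipates post-embolization syndrome, so such a criterion would count expected minor effects.

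**Cost.** The criterion becomes harder to meet, or its stated power falls. As an illustration only, a 10% limit at n = 120 allows at most 5 events (upper limit 9.5%; 6 events give 10.6%). Its power is P(X ≤ 5): 97% at a true rate of 2%, 85% at 3%, but 44% at the plan's own 5%. At that 5%, the Step 1 formula with p0 = 0.10 needs 301 patients for 90% power, so keeping n = 120 means accepting whatever power results.

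The article reports 36 participants by August 2022, beyond the 20-patient safety review. Changing a success criterion at this stage must be documented as an amendment, with its date and reasons.
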